### 8.5.2 Planned Methods for Analysis

The primary endpoint will be analysed by means of a generalized mixed linear model with binomial link function incorporating randomisation arm as fixed and centers as random effects. Odds ratios are calculated as effect sizes incl. 95% confidence interval (CI) and tested. In secondary analysis, the cessation rates are tested by  $\chi^2$  test. Cessation rates and their difference with 95% CI following Wilson (Newcombe 1998b, 1998a) are calculated.

Other event rates are estimated with 95% CI (Wilson) and possibly are compared by chi-squared test without continuity correction and by mid-p test if expected numbers are too small, respectively. Time-to-cessation is analysed by time-to-event methods (Kaplan-Meier estimates and logrank test).

Latency between start of SE and 1) application of the last benzodiazepines before the start of study medication and 2) start of study medication is analysed by descriptive statistics for CSE and NCSE separately. An adjustment of the primary analysis for these covariates will be considered.

(Generalized) mixed linear models are built for the other endpoints (e.g. questionnaire scores) as well for longitudinal analyses similar to the primary endpoint.

In secondary analysis, the inclusion of the Status Epilepticus Severity Score (STESS, Rosetti et al. 2008) into multiple models for several endpoints is envisaged.

Explorative subgroup analyses are performed for female / male patients, generalized or focal CSE with impaired consciousness/ focal CSE without impaired consciousness / NCSE with coma / NCSE without coma. Although the trial is not powered for these comparisons, the analyses will give valuable new insights on the subtypes of SE and elderly patients.

Due to the short period the patient is in the study, we expect that missing data will be a minor problem. Multiple imputation is envisaged only if a high proportion of questionnaire data is missing. The definition and calculation of derived variables as well as a detailed description of the analysis method is stipulated in the statistical analysis plan. It will be established when data from 10% of the patients are input into the database. This proportion is absolutely necessary to take main properties and relationships of the data into consideration.

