|                |                                                                                                                                                                                                                                                                                                                                                                                                                                                                                                                                                                                                                                                                                                                                                                                                                               |
|----------------|-------------------------------------------------------------------------------------------------------------------------------------------------------------------------------------------------------------------------------------------------------------------------------------------------------------------------------------------------------------------------------------------------------------------------------------------------------------------------------------------------------------------------------------------------------------------------------------------------------------------------------------------------------------------------------------------------------------------------------------------------------------------------------------------------------------------------------|
| Biometry       | 
Efficacy: Generalised linear mixed model including randomisation strata as covariate and trial site as random intercept, estimation of odds ratio and rate difference with 95% confidence interval (CI).
 
Description of the primary efficacy analysis and population:
 
Full analysis set (FAS): all patients who received the trial medication will be analysed as randomized (intention-to-treat principle)
 
Safety: Frequencies with 95% CI of complication rates and (S)AEs
 
Secondary endpoints: Event rates (incl. 95% CI), chi test, time to cessation of SE by time-to-event methods, (generalized) mixed linear models for longitudinal analyses as well for the other endpoints (e.g. questionnaire scores) similar to the primary endpoint.
 |

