# 8 BIOMETRY

## 8.1 Biometrical Aspects of the Trial Design

### 8.1.1 Measures to Prevent Bias

#### Randomisation

Randomisation in a 1:1 ratio is performed as block randomisation with randomly varying block length stratified by centre.

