#### Safety

- Mortality
- Need for any emergency medication (different from allocated study drug) during 60 minutes after initiation of study intervention
- Need for ventilation (noninvasive/ invasive) during 60 minutes after initiation of intervention
- ~~Number of patients with SE-associated ventilation until hospital discharge~~
- Intrahospital complications
  - Incidence of delirium as diagnosed by the treating physician
  - Infections requiring intravenous administration of anti-infectives
  - Adverse events related to infusion/subsequent therapy with antiepileptic drug (sedation, dizziness, nausea, vomiting, thrombocytopenia, leukopenia, hypotension, new elevation of liver enzymes, hyperammonaemia, acute new liver failure or pancreatic damage, tremor, psychiatric abnormalities)

The mRS is the recommended outcome measure in stroke trials as it is directly relevant to the patient's ability to return to daily life. Its scores range from 0 (no impairment) to 6 (death) and include special items as walking and independence that are indicative of the degree to which a patient is competent to participate in daily activities (Lees et al. 2012). As most of the seizures occurring in elder people are caused by an underlying structural brain injury the clinical phenomenology of focal convulsive SE or nonconvulsive SE may imitate stroke-related deficits. Thus, the effects on functional outcome may be quantified meaningfully and appropriately by the mRS. The Barthel Index is also a well-established clinicometric scale which is utilized to reflect elderly patient's need for care in particular and includes basic activities such as transfer and personal hygiene (Mahoney and Barthel 1965).

The secondary endpoints will provide valuable insights into the disorder in this age group. There is a special emphasis on characteristics of SE and concomitant intrahospital complications to provide an equal evaluation of the efficacy and safety of antiepileptic treatment in the elderly.

The combination and comparison of the retrospective and prospective assessment of mRS and BI are chosen in order to quantify its consequences on functional outcome.

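### Randomisation is stratified by centre, but other binary secondary and safety event rates are compared by tests that ignore centre: a valid but potentially conservative choice with a simple improvement

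*Protocol*

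**What the plan says.** Section 8.1.1 of the protocol: "Randomisation in a 1:1 ratio is performed as block randomisation with randomly varying block length stratified by centre". Section 3.3 plans about 25 sites.

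Section 8.5.2 gives the primary endpoint a generalised mixed model "incorporating randomisation arm as fixed and centers as random effects". As secondary analysis, cessation is also tested by chi-squared, and the section plans "Cessation rates and their difference with 95% CI following Wilson", a calculation without centre. Other event rates get Wilson intervals and "possibly are compared by chi-squared test without continuity correction and by mid-p test if expected numbers are too small". A later sentence of the same section reads: "Generalized) mixed linear models are built for the other endpoints (e.g. questionnaire scores) as well for longitudinal analyses similar to the primary endpoint".

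The Biometry row of the English synopsis gives secondary endpoints "Event rates (incl. 95% CI), chi 2 test, time to cessation of SE by time-to-event methods". Its efficacy sentence names the mixed model and then "estimation of odds ratio and rate difference with 95% confidence interval (CI"). The German synopsis assigns chi-squared to event rates, mixed models to continuous variables including questionnaire scores, and (generalised) mixed models to longitudinal analyses.

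The binary endpoints in 8.2.2 include ventilation, emergency medication, infections treated with intravenous anti-infectives, mortality and "Incidence of delirium as diagnosed by the treating physician".

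**The concern.** Blocking within centre balances the arms inside each centre, so differences in event rate between centres largely drop out of the arm comparison. A crude chi-squared test still counts those differences in its variance. Its standard error is then too large, it rejects less often than 5% under the null hypothesis, and it loses power.

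Delirium diagnosis, ventilation and the use of intravenous anti-infectives can plausibly depend on local practice. Section 1.2.1 says that an efficacy advantage of one drug may be offset by a better safety profile of the other. A conservative safety comparison leans towards finding no difference, which does not help that weighing.

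A second, smaller matter is consistency. The synopses mention the cessation-rate difference in the same sentence as the mixed model, while 8.5.2 computes it without centre.

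**Working it through.** **The plan's own figure.** Inputs from 8.4: 60% v 47%, two-sided 5%, power 80%. With unpooled variance, n per arm = (1.960 + 0.842)² × (0.60×0.40 + 0.47×0.53) / 0.13² = 7.849 × 0.4891 / 0.0169 = 227.15. Two arms give 454.3, so the stated 454 is reproduced and is used as N below.

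**Why the test becomes conservative.** The crude statistic divides by √[p(1−p)(1/n₁ + 1/n₀)]. With the arms balanced within centres, the true variance is about (1 − ICC) times that quantity, where ICC is the share of outcome variance lying between centres. Hence

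true type I error ≈ 2 × [1 − Φ(1.96 / √(1 − ICC))].

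This gives 4.4% at ICC 0.05, 3.4% at 0.15 and 2.8% at 0.20.

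**Simulation.** From the documents: N = 454, 25 centres, 1:1 blocks within centre, two-sided 5%. Assumed, because the documents give no values: the event rate, the odds ratio, the block size and the SD of centre effects on the logit scale. The crude chi-squared test is compared with a Mantel-Haenszel test stratified by centre.

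Event rate 25%, within-centre odds ratio 1.7, blocks of 4, 40,000 trials per setting:

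| SD (ICC) | Type I error, crude | Type I error, stratified | Power, crude | Power, stratified | Loss (points) |
|---|---|---|---|---|---|
| 0 (0) | 4.8% | 4.9% | 73.7% | 73.4% | −0.3 |
| 0.5 (0.04) | 4.5% | 4.9% | 69.4% | 70.9% | 1.5 |
| 1.0 (0.15) | 3.5% | 5.0% | 59.4% | 65.4% | 6.0 |
| 1.5 (0.26) | 2.5% | 4.9% | 46.2% | 58.7% | 12.5 |

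The simulated type I errors agree closely with the formula. Unequal centre sizes change little.

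A second simulation used unequal centres, an event rate of about 30%, odds ratio 1.8 and 20,000 trials per setting:

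| SD | Type I error, crude | Type I error, stratified | Power, crude | Power, stratified | Loss (points) |
|---|---|---|---|---|---|
| 0 | – | – | 85.1% | 84.9% | −0.2 |
| 0.5 | 4.8% | 5.4% | 81.6% | 82.7% | 1.1 |
| 1.0 | 3.6% | 5.1% | 72.4% | 77.6% | 5.2 |
| 1.5 | 2.4% | 4.9% | 59.0% | 70.7% | 11.7 |

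For scale: at SD 1.0 and a rate of about 30%, 80% of centres have true rates between 9% and 57%.

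**Rare events.** At an event rate of 10% and odds ratio 1.7, power (crude v stratified) is 45.1% v 45.7% at SD 0.5, 38.3% v 41.9% at SD 1.0 and 29.7% v 37.4% at SD 1.5. The losses are 0.6, 3.6 and 7.7 points, and power is below 50% with either test.

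**Cessation-rate difference.** At 60% v 47% (1,500 trials per setting), the crude Newcombe interval covers about 95.5–96%. It disagrees with the mixed-model test in 0.2% to 3.4% of trials for SD 0.3 to 0.8.

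**The case against.** Much of the opposing case stands.

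- **The comparison is optional and exploratory.** Section 8.5.2 says only that it may be made. Section 8.4 calls the secondary analyses mainly explorative and sets no power target. For safety, the synopses promise only frequencies with intervals.
- **A centre-adjusted analysis may already be intended.** The mixed-model sentence in 8.5.2 covers the other endpoints and gives questionnaire scores only as an example. That reading is possible, but the sentence follows one that has already given event rates their own test, and the German synopsis keeps chi-squared for event rates. The assignment is unclear at best.
- **The size is assumed.** Nothing in the documents supports an SD of 1.0 or more. Section 8.1.1 works against a wide spread for some endpoints, since infections are defined in working instructions and teams are trained. Mortality is not obviously practice-driven.
- **Sparse strata are a real reason for a simple test.** With about 18 patients per centre (454/25), rare events leave many centres uninformative.
- **The evidence for the remedy is for Mantel-Haenszel.** The mixed model was not simulated at these lower event rates.

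A reader might infer that the planned safety tests are invalid, or that the safety intervals are too wide. The documents support neither. The error is on the conservative side, and 8.5.2 plans intervals for the rates of other events but specifies none for their differences. The only crude difference interval specified is the one for cessation, where the effect is small.

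The SAP may add detail, but it does not remove the point, because the protocol itself names a test without centre.

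**Conclusion.** The point holds as a minor efficiency and consistency improvement. The direction is well supported: the formula and two simulations with different settings agree that the crude test loses power as centres differ, while the stratified test stays close to 5% and costs 0.7 points or less when centres do not differ (the largest cost, at a 47% event rate, is 80.7% v 80.1% before rounding).

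The size is uncertain. At event rates of 25–30% the loss is about 0 to 1.5 points at SD 0 to 0.5, 5 to 6 points at SD 1.0 (type I error about 3.5%) and 12 to 13 points at SD 1.5 (about 2.5%). Which of these applies to this trial cannot be read from the documents. It would therefore go too far to say that real safety differences will be missed, or that power is given away for no reason. The primary test is unaffected and there is no added risk of false positives.

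**What to change.** In 8.5.2 and both synopses, state that where binary secondary and safety endpoints are compared between arms, a centre-stratified Mantel-Haenszel test or the centre-adjusted mixed model of the primary endpoint is used, with a mid-p (exact) test as fallback for sparse events. Keep crude rates with Wilson intervals as description.

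Name one method for the cessation-rate difference and its interval, preferably stratified by centre or standardised from the primary model, and use it consistently in the Biometry rows of both synopses and in 8.5.2.

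The cost is one paragraph in 8.5.2 with matching lines in the synopses. No new data are needed, and precision is practically unchanged if centres turn out alike.

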| Biometrie     | 
Wirksamkeit: Verallgemeinertes gemischt-lineares Modell mit Randomisations-Strata als Kovariaten und Studienzentrum als zufälliger Konstante; Schätzung des Odds Ratios und der Differenz der Häufigkeiten mit 95% Konfidenzintervall (CI).
 
Beschreibung der primären Wirksamkeitsanalyse und Population
 
Full analysis set (FAS): Alle Patienten, welche die Studienmedikation erhielten, werden wie randomisiert analysiert (intention-to-treat Prinzip)
 
Sicherheit: Häufigkeiten der Komplikationsraten and (S)AEs mit 95% CI
 
Sekundäre Endpunktes: Eventraten (inkl. 95% CI), Chi-Test, Zeit bis Durchbrechen des SE: Kaplan-Meier-Schätzer und Cox-Regression, geschätztes Hazard Ratio inkl. 95% CI.
 
Kontinuierliche Variablen (inkl. Fragebögen-Scores): gemischt-lineare Modelle, Schätzung der mittleren Differenzen inkl. CI
                                                                                                                                                                                                                                                                                                                                                                                                                                                                                                                                                                                                            |

|          |                                                                                                                                                                                                                                                                                                                                                                           |
|----------|---------------------------------------------------------------------------------------------------------------------------------------------------------------------------------------------------------------------------------------------------------------------------------------------------------------------------------------------------------------------------|

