### 4.3 Justification for the Inclusion of vulnerable Populations

As outlined above, SE is a potentially life-threatening condition with overall mortality rates of 20% (Trinka and Kälviäinen 2017). As the outcome of SE worsens with the duration of the condition, patients with SE, in particular those with generalized convulsive SE and focal convulsive SE with impairment of consciousness require immediate medical treatment. In case of nonconvulsive SE there is growing evidence that it results in high morbidity and mortality (DeAssis et al. 2012) so treatment should also not be delayed and start as soon as possible. Due to the nature of the disorder and due to the requirement, as per definition, of failed prior therapy with benzodiazepines, patients with established SE are unable to provide informed consent before the initiation of the trial therapy, neither verbally nor in writing.

Considering the present scientific evidence and clinical practice, the trial offers the so far best available treatment of established SE in the elderly; it also reflects recommendations of international guidelines and takes into account age-related biological characteristics. Drug treatment within this trial is almost certain to be substantially safer as the recommended therapy, which places phenytoin first, regardless of age, and hence exposes elderly patients to considerable risks. Furthermore, as there are insufficient data to justify the choice of one treatment over the other, any of the two drugs, LEV and VAL, can be considered as the best.

Patients included in this trial will benefit from the fact that treating physicians will be educated about recognising SE and its medical treatment.

The following describes the general procedure for obtaining informed consent in the special patient population of this trial; the SE related specifics will be listed and explained for each point:

**1) Patients with generalized convulsive SE or focal convulsive SE with impairment of consciousness** suffer from a life-threatening condition and must be treated immediately. In order to avoid an unacceptable delay of treatment the patient will be included in the trial according to § 41 (1) AMG. The treating physician decides about the inclusion while regarding inclusion and exclusion criteria.

The involvement of an independent medical consultant **can't be considered** as this would cause an unethical delay in therapy in this life-threatening condition. This procedure

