**Visit 2 (V2)****Day of discharge/day before discharge from hospital or day 30 (+/- 1 day), whatever is sooner**

- Record the following data (eCRF)
  - day of recurrence of seizures or convulsive SE after successful intervention/ day of detection of NCSE (EEG) after successful intervention
  - day of first EEG-detection of terminated NCSE after failed intervention
  - further antiepileptic treatment after intervention: medication, dosage, type and frequency of application including stop of medications
  - reason for withdrawal of treatment with VPA or LEV
  - acute renal failure with or without dialysis
  - acute pancreatitis
  - acute hepatic failure
  - lab analysis: level of ammoniaemia and subsequent repetitions, as ordered by treating physician \*
  - type of infections requiring i.v. antibiotic treatment
  - start and stop of invasive/noninvasive ventilation (day)
  - development of delirium and treatment
  - complications requiring surgery or invasive diagnostics/ therapy
  - etiology of SE (cerebral focus, metabolic/infectious/toxic conditions, noncompliance/withdrawal/change of antiepileptic medication)
  - home care after hospital stay (if applicable)
- Administer GCS and perform brief neurological exam: orientation, horizontal extraocular movements, motor drift of both arms and legs, sensation, language.
- Obtain mRS and BI

\* **NOTE:** As soon as an otherwise unexplained disturbance of consciousness, nausea or hypotension occurs in duration of treatment with VPA during the hospital stay the efforts of clarification **must** include the detection of a potential hyperammonemia.

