**Termination of trial therapy does not mean that the patient is off-trial.**

### 6.4.2 Premature trial termination for individual patients

All randomised patients will be followed up until Visit 2. Premature termination of trial therapy does not necessarily lead to individual trial termination (see chapter 6.4.1 for explanation).

The only circumstances in which a premature trial termination (i.e. no further trial visits) in a randomised patient is unavoidable are:

- The clinical condition of a patient is worsening (and not responding to treatment) that contraindicates permanently participation in any trial visits

- withdrawal of informed consent or
- death of the patient.

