#### Efficacy

- Time from initiation of trial intervention to cessation of eSE within 60 minutes
- Neurological status (including vigilance) 60 minutes after initiation of intervention

- Difference of blood levels of VPA and LEV before and 60 minutes after initiation of intervention
- Recurrence of seizures or nonconvulsive/ convulsive SE after initially successful intervention
- For patients who failed the primary endpoint, number of patients in whom SE ceased during 60 minutes after initiation of intervention according to the treating physician
- For NCSE patients who failed the primary endpoint, time to first cessation, as verified by EEG
- Number of patients with SE-associated ventilation until hospital discharge
- Functional outcome at discharge, defined by Barthel Index (BI) and modified Rankin Scale (mRS)

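### Kaplan-Meier is the only method named for time to EEG-verified cessation in failed NCSE, and death is not addressed; if deaths are censored, cessation is overstated

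*Protocol*

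**What the plan says.** The efficacy list in Section 8.2.2 of the protocol has two times to cessation:

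- "Time from initiation of trial intervention to cessation of eSE within 60 minutes", for all patients.
- "For NCSE patients who failed the primary endpoint, time to first cessation, as verified by EEG".

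The second has no time limit in its definition. Visit 2 in Section 6.3 shows how it is captured: the eCRF records the "day of first EEG-detection of terminated NCSE after failed intervention", and the visit takes place on "Day of discharge/day before discharge from hospital or day 30 (+/- 1 day), whatever is sooner". It is therefore an in-hospital time in days.

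Section 8.5.2 gives one method sentence: "Time-to-cessation is analysed by time-to-event methods (Kaplan-Meier estimates and logrank test". It does not separate the two endpoints. The German synopsis has "Zeit bis Durchbrechen des SE: Kaplan-Meier-Schätzer und Cox-Regression", and the English synopsis refers only to time-to-event methods in general. No competing-risk method is named, and no censoring rule is stated.

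On mortality, Section 4.3 says "SE is a potentially life-threatening condition with overall mortality rates of 20" percent, and Section 1.1 cites case fatality of up to 50% over age 80. Section 6.4.2 lists "death of the patient" among the unavoidable reasons for leaving the trial early.

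**The concern.** A patient who dies in NCSE can never reach EEG-verified cessation. Usual Kaplan-Meier practice censors that patient on the day of death, and so assumes that the NCSE would later have stopped at the same rate as in those still alive. One minus the curve then estimates cessation in a world without death. It is easily read as the share of failed NCSE patients whose status was eventually stopped, and it is larger than that share whenever deaths occur first.

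The excess grows with the number of early deaths. Two arms with the same true share of stopped NCSE but different early mortality would show different curves, and the arm with more deaths would look better. Section 1.2.1 expects that an efficacy advantage of one drug may have to be weighed against better safety of the other. An efficacy estimate raised by deaths would blur that comparison.

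**Working it through.** **The plan's own figures.** The protocol gives no figure for this endpoint. The nearest is the sample size, used here only to gauge how many patients are involved. With success rates of 60% and 47%, two-sided 5% and 80% power, the unpooled formula gives (1.960 + 0.842)² × (0.60 × 0.40 + 0.47 × 0.53) / 0.13² = 227.2 per arm. Rounded to 227, this reproduces the stated 454.

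**Patients concerned.** Expected failures are 227 × 0.40 + 227 × 0.53 = 90.8 + 120.3 = 211. The NCSE share is not given. Assuming 30% to 50%, there are 63 to 106 NCSE failures: about 27 to 45 on VPA and 36 to 60 on LEV.

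**Model.** Assume constant daily hazards of cessation (c) and of death before cessation (d) over 30 days, with no other censoring.

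- True share stopped (cumulative incidence): c/(c + d) × (1 − exp(−30(c + d)))
- One minus Kaplan-Meier with deaths censored: 1 − exp(−30c)

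**Check A: fix the day-30 shares.** For true cessation 75% and 10% dying first, 30(c + d) = −ln(0.15) = 1.897. Then 30c = 1.897 × 0.75/0.85 = 1.674, and 1 − exp(−1.674) = 81.2%, an excess of 6.2 points. Other splits, as excess in points:

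| Die before cessation | True 40% | True 50% | True 60% | True 70% | True 75% |
|---|---|---|---|---|---|
| 5% | 1.2 | 1.6 | 2.1 | 2.6 | 2.9 |
| 10% | 2.6 | 3.4 | 4.4 | 5.5 | 6.2 |
| 20% | 5.7 | 7.7 | 10.1 | 13.3 | not run |

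At 15% dying first and true cessation 75%, the estimate is 85.3% (+10.3).

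**Check B: use the cited mortality as a 30-day death hazard.** Here d = −ln(1 − mortality)/30 and c = ln 2/median days to cessation.

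| Mortality | Median 1 day | 3 days | 7 days | 14 days |
|---|---|---|---|---|
| 20% | 1.1 | 3.1 | 5.7 | 6.2 |
| 50% | 3.2 | 9.0 | 15.9 | 16.9 |

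**Difference between arms.** If both arms truly stop NCSE in 75%, but 5% die first in one and 15% in the other, the estimates are 77.9% and 85.3%. The gap of 85.3 − 77.9 = 7.4 points favours the arm with more deaths.

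**Against sampling error.** At 75%, the per-arm standard error is √(0.75 × 0.25/n): 8.3 points at n = 27 and 5.6 points at n = 60. The 6.2-point excess is then 6.2/8.3 = 0.75 to 6.2/5.6 = 1.1 standard errors.

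**The case against.** The strongest reply has four parts.

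1. **Censoring is not stated.** A reader might infer that the protocol treats death before cessation as censoring, so that the reported rate is bound to be too high. The document does not say so. Nor is censoring the only option: if deaths are kept in the risk set as event-free to day 30 and nothing else is censored, one minus Kaplan-Meier equals the cumulative incidence. Section 8.5.2 leaves derived variables and method detail to the SAP, which is not shown. This stands, and it makes the point conditional.

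2. **The sentence may be meant for the 60-minute endpoint.** It is generic, and Section 8.2.1 also speaks of time to cessation within the primary 60-minute definition. This is possible. But the sentence carries no such limit, and the method left for the other endpoints, (generalized) mixed linear models, does not suit a censored time. Kaplan-Meier is the only named method that fits.

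3. **The size is assumed.** The 20% and 50% describe SE overall and the very old, not deaths before EEG-verified cessation in NCSE failures. Further treatment follows a failure, so quick cessation is plausible, and the excess is then small. This stands.

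4. **Little depends on it.** Section 8.4 calls the secondary analysis mainly explorative, mortality is reported separately, and the logrank test remains valid as a comparison of cause-specific hazards. This stands too, and it sets the priority.

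Deferral to the SAP does not dispose of the point. The protocol already names an estimator whose standard use overstates cessation when death precludes it.

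**Conclusion.** The point holds in conditional form. The protocol names Kaplan-Meier with logrank for an in-hospital time to cessation, in a population with substantial cited mortality, and does not address death. If deaths before cessation are censored, the share whose NCSE stopped is overstated, and for equal true shares it is overstated more in the arm with more early deaths.

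The size is not derivable from the document. Under constant hazards and assumed splits:

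- about 1 to 3 points if at most 5% die first, or if mortality is 20% and median cessation is 1 to 3 days;
- about 3 to 6 points if 10% die first, the upper end requiring true cessation of 75%;
- about 6 points or more if 20% die first.

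The document does not support the reading that the overstatement is certain or large. It also does not support any doubt about the primary result, which this leaves untouched. This is a low-priority improvement to an exploratory secondary endpoint in a subgroup defined after randomisation.

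**What to change.** In Section 8.5.2:

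- Limit Kaplan-Meier to the 60-minute endpoint.
- For EEG-verified cessation in NCSE patients who failed the primary endpoint, report the cumulative incidence (Aalen-Johansen) per arm, with death before cessation as the competing event and its own curve shown alongside.
- Keep the logrank test for this endpoint, labelled as a comparison of cause-specific hazards.
- State how discharge with ongoing NCSE is handled, since that is a second possible source of informative censoring.

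The cost is a sentence or two. No new data are needed: mortality is already an endpoint, and the end-of-study form in Section 6.4 records the date and reason. The downside is that the reported cessation rate becomes somewhat lower than a Kaplan-Meier figure with deaths censored.
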